### Allocation of intervention

Buildings will be organized into comparable pairs based on geographic, resource, and demographic characteristics. Each building pair will be allocated to receive or not receive the intervention (1:1 ratio) via computer-generated paired randomization by a statistician not affiliated with the project.

### Assessment measures

#### Primary and secondary outcome measures

For the composite primary outcome, we will compare the healthcare utilization of intervention and control buildings as measured by:
Change in the monthly rate of CVD-related ED visits from 1 year pre intervention to 1 year post interventionChange in the monthly rate of CVD-related hospitalization from 1 year pre intervention to 1 year post intervention.

Secondary outcome measures will include:
Difference in unplanned all-cause healthcare utilization, measured by unplanned all-cause ED visit rates and unplanned all-cause hospitalization rates between intervention and control group from 1 year pre intervention to 1 year post interventionDifference in the quality of life and QALYs (measured by the EQ-5D-5L) in CHAP participants from baseline to 1 year post interventionCost-effectiveness, based on program cost of implementing CHAP for 1 year in subsidized seniors’ housing buildings and measured outcomesParticipants’ experience of the CHAP intervention (qualitative).

Other pre-specified outcome measures include:
Change in BP among CHAP participants from baseline to 1 year post interventionChange in BMI from baseline to 1 year post interventionChange in waist circumference from baseline to 1 year post interventionChange in Canadian Diabetes Risk (CANRISK) Questionnaire score measured using the baseline to 1year post intervention.

#### Process evaluation measures

Process evaluation measures will include resident participation rates (number of participants attending CHAP sessions, number of participants attending education sessions, including initial attendance and repeat visits), information on volunteers (number trained, number of sessions volunteered), program delivery (e.g., completion of risk assessments), and other program evaluation measures (e.g., detection rates for hypertension and diabetes, number of feedback reports sent to family doctors).

Key informant interviews or focus groups will be conducted post intervention with the CHAP volunteers, housing authorities, participants, and non-participants regarding strengths, weaknesses, and opportunities to improve and sustain the program.

### Intervention

The CHAP sessions will be voluntary drop-in clinics conducted by trained volunteers following pre-specified protocols and supervised by a research nurse to ensure intervention fidelity. Volunteers will be trained in person by CHAP research staff on research processes (privacy/confidentiality, obtaining informed consent), participant assessment, data collection, and use of algorithms to refer participants to the health nurse (see Additional files 2 and 3). The sessions will be delivered in a common space within each intervention building. Sessions will include:
BP readings using a validated automated BP machine during each monthly CHAP sessionThe validated CANRISK diabetes risk questionnaire [25], which measures cardiometabolic risk factors such as BMI, waist circumference, diabetes history, smoking, diet, physical activity, and smokingHealthy lifestyle and preventive care materials (e.g., pamphlets)Invitation to participate in group health education following each monthly CHAP session. The health education sessions will include common health-related topics and will be delivered by local expert community organizations. The health education is not a standardized program (pragmatic), and it is expected that there will be heterogeneity between communities and buildingsUpon participant’s consent, blood pressure, BMI, waist circumference and CANRISK score sent to family doctor.

All tenants in intervention buildings will be invited to participate in CHAP sessions and subsequent education sessions using multiple recruitment strategies, including posters in common areas. Participation is voluntary, and all participants will provide written informed consent for their individual-level data to be collected (see Additional file 4).

The control buildings will receive usual care, which will be any wellness programs if already present in the building prior to the RCT. Not all control buildings will have wellness programs.

### Data collection

Data during the CHAP intervention session will be collected either on paper or through an electronic form. All data collected will be protected and kept confidential. Paper forms will be kept in locked cabinets in the research office. All data in the electronic platform will be kept in encrypted and firewall-protected servers only accessible to the research team, volunteers, and nurses implementing the program. All data analysis of collected data will be anonymized.

The primary outcomes will be assessed using de-identified administrative datasets in Ontario and Quebec. We will use building-level data for each of these outcomes, at monthly intervals for 1 year prior to and for the 1-year duration of the program.

Quality of life data will be collected using the EQ-5D-5 L, administered by a research assistant or volunteer to all residents of intervention buildings who attend a CHAP session. This will be done at two time points, when the participants attend their first CHAP session and then at the final CHAP session. Cost-effectiveness will be calculated by collection of program cost data and health outcomes. Health experiences and perceptions of participants will be collected at the end of the study by a trained research assistant using four qualitative focus groups of intervention residents, including two in Ontario and two in Quebec.

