### Control of bias and loss to follow-up

This will be an open trial with no blinding or masking. Due to the nature of the health intervention (health sessions in intervention buildings), it will not be possible to blind participants as to whether they are receiving the intervention or not. However, since randomization is at the building level and the primary outcome (ED visit rates and hospital admission rates) is at a cluster level and collected from administrative data sources, the study will be less prone to social desirability bias. No consent for the primary outcome will be collected from the intervention and control building residents since it will be based on de-identified administrative data. Consent will only be collected from building residents who attend the CHAP sessions for their participation in the CHAP sessions.

Since the primary outcome is being analyzed at the building level, we anticipate no loss to follow-up for healthcare utilization data. We will retrospectively assess residents who lived in the intervention and control buildings at the pre- and post-intervention periods. There may be movement of residents in and out of the buildings; however, this will likely happen in both intervention and control buildings. This is expected to be balanced between the intervention and control arms. For the secondary outcome measures that require collection of data directly from residents, loss to follow-up is anticipated to be 40% [24]. A previous study conducted in this subsidized housing population found that there was a higher rate of deaths, relocations, and inability to contact in this population compared to the general population [21, 24]. However, we assume that losses to follow-up will be similar between the intervention and control groups.

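### The follow-up EQ-5D-5L is tied to attendance at the final drop-in session, so enrolled residents who stop attending have no 1-year quality-of-life value

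*Protocol article*

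**What the plan says.** All places are in the protocol article.

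- **Data collection.** The EQ-5D-5L is "administered by a research assistant or volunteer to all residents of intervention buildings who attend a CHAP session". On timing: "This will be done at two time points, when the participants attend their first CHAP session and then at the final CHAP session".
- **Intervention.** "The CHAP sessions will be voluntary drop-in clinics", held monthly, with no obligation to return. Those who take part give written consent for individual-level data.
- **Primary and secondary outcome measures.** The secondary outcome is the change in quality of life and QALYs in CHAP participants between baseline and 1 year.
- **Study aims.** The same objective is worded around participants who attend the sessions over the year.
- **Quantitative data.** Quality of life and QALYs are to be analysed by intention to treat, using GEE. Multiple imputation with five imputations applies if more than 5% of follow-up outcome data are missing.
- **Control of bias and loss to follow-up.** "For the secondary outcome measures that require collection of data directly from residents, loss to follow-up is anticipated to be 40"%, with a citation to an earlier study. The next sentence says that previous work found that "there was a higher rate of deaths, relocations, and inability to contact in this population compared to the general population".

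**The concern.** The only stated occasion for the second EQ-5D-5L is a session that nobody is obliged to attend. Leaving the programme therefore also ends outcome measurement, even for a resident who is alive, at the same address and willing to answer. Whether a value exists then depends on continued engagement with the intervention being evaluated.

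What is at stake is the meaning of the quality-of-life and QALY result. It is a before-after comparison within intervention buildings and has no control series to absorb selection. If people stop because of illness, frailty or dissatisfaction, the observed change describes those who did well enough to keep coming. The 40% anticipated loss does not settle the matter, because the section that states it never mentions non-attendance.

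**Working it through.** **1. Does either reading of the timing rule reach those who stop?**

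- *Final session means the building's last session.* Anyone who has stopped, or is absent that day, is missed.
- *Final session means each participant's own last visit.* In a drop-in programme nobody knows at the time that a visit is the last. For an early stopper the value would not be a 1-year value in any case.

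Under neither reading does a resident who has stopped attending get a 1-year EQ-5D-5L.

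**2. Does this fit the outcome and the analysis?** The outcome is defined in CHAP participants over a year, and the analysis is by intention to treat. Both point to everyone enrolled. The collection rule delivers only those still attending. The Study aims wording is closer to the collection rule, so the sections do not agree on who is being described.

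**3. Can imputation repair it?** The 5% trigger would be met unless final-session attendance were at least 95%. EQ-5D-5L is taken at two points only, so no quality-of-life value is observed after a person stops. The imputation model must predict values for those who stopped from people who continued, under missing-at-random. If stopping depends on health after the last visit, that assumption fails, and these data cannot test it.

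**4. How much would be missing?** The 40% is a cited assumption without a derivation, so it cannot be reproduced. The documents give no attendance rate for the final session. Let a be that rate (assumed). There are two cases:

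- Non-attendance *replaces* the 40%, with a taken among all enrolled: missing = 1 − a.
- Non-attendance *adds to* the 40%, with a taken among the remaining 60%: missing = 1 − 0.6a.

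| a (assumed) | 1 − a | 1 − 0.6a |
|---|---|---|
| 75% | 25% | 55% |
| 50% | 50% | 70% |
| 30% | 70% | 82% |

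The stated 40% is matched only at a = 60% in the first case or a = 100% in the second.

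**5. How much bias could follow-up of non-attenders remove?** Let p be the share of reachable participants who attend the final session. Suppose those who stopped have a mean EQ-5D change d worse than attenders, with d = 0.05 (both p and d assumed). Session-only collection observes the attenders' mean. Contact-based follow-up would observe the attenders' mean minus d(1 − p). The difference is d(1 − p):

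- p = 0.9: 0.05 × 0.1 = 0.005
- p = 0.7: 0.05 × 0.3 = 0.015
- p = 0.5: 0.05 × 0.5 = 0.025
- p = 0.3: 0.05 × 0.7 = 0.035

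This compares observed means before any imputation.

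**The case against.** **The analysis already provides for missing data.** Imputation is planned, repeat attendance is recorded, and blood pressure and other risk measures are taken at sessions, so an imputation model would have something to work with. This stands in part: such variables make missing-at-random more plausible. They do not show what happened to a person's health after the last visit.

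**The aim may be attenders only.** The Study aims wording can be read that way. If so, collection at the last session is coherent, but the outcome definition and the intention-to-treat commitment then need to be brought into line with it.

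**An article condenses the full protocol.** Tracing of absentees may be described elsewhere, and the analysis section does speak of a follow-up survey. However, the point is not about an omitted detail: the article states when and where the second measurement happens, and that rule is what ties it to attendance.

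**The consequence is limited.** This stands. The outcome is secondary and uncontrolled. The primary outcome comes from administrative data, and the cost-effectiveness analysis is described as resting on administrative data and programme costs.

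Three stronger readings are tempting but not supported:

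- A reader might infer that the 40% comes from a study that actively sought people out, so that true loss must exceed it. The cited study's procedure is not shown. The sentence on deaths, moves and lost contact compares this population with the general population; it does not say that these make up the 40%. At 75% attendance, with non-attendance replacing the 40%, only 25% would be missing.
- A reader might multiply 0.05 by the whole missing share, for example 0.46 to 0.82, and report a bias of 0.023 to 0.041. Those shares include the 40% taken as unreachable, whom no change to the collection rule would recover.
- A reader might conclude that the result is necessarily too favourable. Healthy residents who see no need to return may also stop.

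**Conclusion.** The concern holds for the EQ-5D-5L and QALY outcome: the stated rule makes 1-year measurement conditional on attending one voluntary session, and that does not match the outcome definition or the intention-to-treat analysis. The primary outcome is not touched.

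The size cannot be fixed from the documents. Across assumed attendance of 75% and 50%, missing data are 25% and 50% if non-attendance replaces the stated 40%, and 55% and 70% if it adds to it. Which case applies is not shown. On an assumed 0.05 worse change in those who stopped, the removable bias is 0.005 to 0.035 for p from 0.9 to 0.3. Selection of healthier or more satisfied attenders is plausible, but its direction is not established.

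**What to change.** In Data collection, replace the reference to the final session with one fixed end-of-programme window for each building. Within it, research staff seek the EQ-5D-5L, in the building or by telephone, from every consented participant who has not withdrawn, whether or not they still attend. Record whether each person was still attending, so that the analysis can compare the two groups and use attendance in the imputation.

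The cost is some extra contacts by existing staff (a research assistant is already named for this task) and a minor amendment to the two ethics boards. The consent form is not shown, so check whether it covers later contact. The change has to be made before the final sessions, because a 1-year value not collected then cannot be recovered.

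If session-only collection is kept, three text changes are needed:

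- State that the anticipated 40% must cover non-attendance, and give a range.
- Limit the quality-of-life and QALY conclusion to residents still attending at the end.
- Reconcile Study aims, the secondary outcome definition and the intention-to-treat statement in Quantitative data.

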### Data analysis plan

#### Quantitative data

We will analyze data with the building or cluster as the primary unit of analysis, rather than the individual. The reason is that it is not possible to acquire individual-level consent from the control building residents to obtain their health administrative data. It is possible to get this information in aggregate form for each building.

The analysis and reporting of the trial will follow the Consolidated Standards of Reporting Trials (CONSORT) extension to cluster trials [26]. The analysis of the baseline characteristics will be based on descriptive statistics reported as count (percent) for categorical variables and mean (SD) or median (first quartile, third quartile) for continuous variables. The analysis of primary and secondary outcomes will follow the intention-to-treat principle. For the primary building-level outcome measure we will analyze the data using analysis of covariance (ANCOVA), adjusting for pairing (fixed-effect) and baseline rate (covariate) in the model. For the secondary individual-level data (quality of life, QALY), we will use the intention-to-treat principle analysis and analyze the data using generalized estimating equations (GEEs) assuming an exchangeable correlation structure to adjust for clustering within a building [27]. Multiple imputation (iterative Markov chain Monte Carlo method) with five imputations will be used if more than 5% of the participant outcome data is missing in the follow-up survey [28]. All analyses will be performed using STATA 11.2.

Since CHAP is a health promotion program that can be integrated into the health system and is expected to impact health system utilization, we will conduct a cost-effectiveness analysis. This analysis will be conducted at a building level and will therefore be based on administrative data and program costs. Therefore, the sample size will be the same as that for the main outcome.

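### Quality of life and QALYs are labelled intention to treat with balanced loss between arms, but EQ-5D-5L is collected only from attendees in intervention buildings, over intervals that can fall short of a year

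*Protocol article*

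**What the plan says.** Four parts of the protocol article bear on this outcome.

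- **Study aims, and Primary and secondary outcome measures.** Both define quality of life and QALYs as the change in people who attend CHAP, measured against their own baseline, over one year. Neither names a control comparison for this outcome.
- **Data collection.** EQ-5D-5L is "administered by a research assistant or volunteer to all residents of intervention buildings who attend a CHAP session". There are two time points: "when the participants attend their first CHAP session and then at the final CHAP session". No other source of EQ-5D-5L data is described.
- **Data analysis plan, Quantitative data.** "For the secondary individual-level data (quality of life, QALY), we will use the intention-to-treat principle analysis". The method is GEE with an exchangeable correlation structure for clustering within buildings, with multiple imputation if more than 5% of follow-up data are missing. A general sentence just before this also applies intention to treat to all primary and secondary outcomes.
- **Control of bias and loss to follow-up.** "Consent will only be collected from building residents who attend the CHAP sessions for their participation in the CHAP sessions". For secondary outcomes collected directly from residents, a 40% loss is anticipated, followed by the reassurance that "we assume that losses to follow-up will be similar between the intervention and control groups".

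On attendance, the Intervention section states: "The CHAP sessions will be voluntary drop-in clinics conducted by trained volunteers". Sessions are monthly.

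**The concern.** Intention to treat means analysing units in the arm to which they were allocated, so that the randomized comparison is kept. Here the measured group is formed after allocation, by residents' own choice to attend, and in one arm only. The label therefore claims a property that the data cannot have. The sentence on similar losses has the same fault: it offers balance between arms as a safeguard where one arm has no data to lose.

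At stake is how the result will be read. Under the current wording, an uncontrolled before-after change in volunteers could be reported as an intention-to-treat secondary outcome of a cluster randomized trial. Such a change can combine any effect of the programme with ageing, regression to the mean and selective return for the second measurement, and the design cannot separate them.

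A second issue concerns time. Baseline is the first drop-in session that a person happens to attend, so the interval to the final session depends on when that person joined, while the outcome is labelled as a one-year change.

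**Working it through.** The article gives no sample size or expected effect for quality of life, so there is no planned figure to reproduce. The check sets sections side by side and then does arithmetic on the interval.

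**1. Who contributes data**

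| Group | EQ-5D-5L collected? | Source |
|---|---|---|
| Control-building residents | No | Data collection; consent limited to attendees (Control of bias) |
| Intervention residents who never attend | No | Data collection |
| Intervention residents who attend | Yes, at first and final session | Data collection |

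Control residents with EQ-5D-5L data = 0, so no between-arm contrast can be formed. GEE handles correlation within intervention buildings, and imputation fills in missing follow-up among attendees. Neither supplies a comparator.

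**2. Share with paired measurements**

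With 40% loss, the observed pairs cover 1 − 0.40 = 60% of attendees. The article gives no expected attendance. If 10% to 50% of intervention residents attend (assumption), pairs cover 0.10 × 0.60 = 6% to 0.50 × 0.60 = 30% of them. In control buildings the share is 0%.

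**3. Length of the interval**

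Assumptions: 12 monthly sessions, with follow-up at session 12. A person first attending at session k then has an interval of 12 − k months, from 11 (k = 1) down to 0 (k = 12). The article gives no distribution of first attendance, so several are shown.

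- Even entry over sessions 1 to 11: (11 + 10 + … + 1)/11 = 66/11 = 6.0 months.
- Even entry over sessions 1 to 12: 66/12 = 5.5 months.
- Even entry over sessions 1 to 3 only: (11 + 10 + 9)/3 = 10.0 months.
- Front-loaded entry, where a fraction q of those not yet enrolled first attends at each session. The weights are q(1 − q)^(k−1) for k = 1 to 12, rescaled to sum to 1:

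| q | Mean interval (months) |
|---|---|
| 0.3 | 8.8 |
| 0.5 | 10.0 |
| 0.7 | 10.6 |

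These figures take the final session to be the programme's last. The wording could also mean the participant's own last session, in which case intervals would be shorter still and more variable.

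**The case against.** The strongest reply is that no randomized quality-of-life effect was ever promised. The aims and the outcome list both say that attendees are compared with their own baseline, so an attentive reader knows that this is a before-after measure. That is correct, and it limits the point: the fault lies in the analysis and bias sections, which contradict the aims. It does not excuse those sections. Intention to treat is applied to quality of life in a sentence of its own, and the loss assumption names a control group.

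A second reply is that unequal intervals are inferred. This also stands in part. All tenants are invited by several routes, so early entry is plausible and the mean interval may be nearer 9 to 11 months than 6. Even so, a drop-in programme with baseline at first attendance cannot guarantee a year for later entrants.

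A third reply is that multiple imputation is planned. It addresses missing follow-up among attendees but does nothing for the missing arm.

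A reader might go further than the article supports:

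- **That QALYs are computed as if everyone had 12 months.** The article does not say how QALYs are calculated.
- **That no change over about a year can be seen.** People who attend the opening session and return at the end give roughly 11 to 12 months, although still uncontrolled and in a subset.
- **That the cost-effectiveness analysis is undermined.** Quantitative data places it at building level, on administrative data and programme costs.
- **That blood pressure, BMI, waist circumference and CANRISK share the fault.** They are listed as other pre-specified measures, outside the contested sentences.

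**Conclusion.** The point holds as a contradiction within the article. For quality of life and QALYs, the intention-to-treat label and the assumption of similar loss between arms cannot apply, because the control arm contributes no data and the intervention arm contributes only self-selected attendees. This conclusion rests on the article's text and needs no assumption.

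The interval issue is real but less certain in size. With 12 monthly sessions and follow-up at the last, the mean is about 5.5 to 6 months under even entry and about 9 to 11 months under early entry. Both the number of sessions and the entry pattern are assumptions.

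The randomized primary outcome, taken from administrative data at building level, is unaffected. The correction should be made because it changes what can be concluded about quality of life, but it concerns a secondary outcome only.

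**What to change.** - **Data analysis plan, Quantitative data.** Remove intention to treat for quality of life and QALYs, and exempt them from the general sentence on secondary outcomes. Describe the analysis as a single-arm before-after change in attendees, with GEE for clustering within intervention buildings, and state that no programme effect will be claimed from it.
- **Control of bias and loss to follow-up.** Delete the between-arm loss assumption for resident-collected outcomes. State instead that the anticipated 40% loss may bias the change seen in attendees.
- **Data collection, and Primary and secondary outcome measures.** Say whether the final session is the programme's last or the participant's own last. Analyse change and QALYs over the time that actually elapsed between the two measurements, and report the distribution of that interval beside the result.

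The cost is wording, plus use of the dates of the two sessions at which EQ-5D-5L is given. No extra measurement or visit is needed. The downside is a weaker claim for quality of life, which is all that this data collection can support.

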**Methods/design:**

This is a pragmatic, cluster randomized controlled trial in community-based social (subsidized) housing buildings in Ontario and Quebec. All residents of 14 matched pairs (intervention/control) of apartment buildings will be included. Buildings with 50–200 apartment units with the majority of residents aged 55+ and a unique postal code are included. All individuals residing within the buildings at the start of the intervention period are included (intention to treat, open cohort). The intervention instrument consists of CHAP screens for high blood pressure using automated blood pressure monitors and for diabetes using the Canadian Diabetes Risk (CANRISK) assessment tool. Monthly drop-in sessions for screening/monitoring are held within a common area of the building. Group health education sessions are also held monthly. Reports are sent to family doctors, and attendees are encouraged to visit their family doctor. The primary outcome measure is monthly CVD-related ED visits and hospitalizations over a 1-year period post randomization. Secondary outcomes are all ED visits, hospitalizations, quality of life, cost-effectiveness, and participant experience.

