### Sample size

For the main outcome (ED visits and hospitalization) we computed the sample size based on the number of ambulatory care-sensitive ED visits from Canadian Institute for Health Information (CIHI) data [23]. The estimated mean number of ED visits for an individual is 0.39 (standard deviation [SD] = 0.12). We assumed that the intervention will lead to 9% difference in the mean number of ED visits by residents of intervention buildings compared to control building residents. This was based on the effect CHAP had on the hospitalization rates in the community cluster RCT [5]. We also assumed an intraclass correlation coefficient (ICC) of 0.07 for our design effect based on data analyzed from previous studies [21, 24]. Using a power of 0.8 and an alpha of 0.05, we will need a total of 1118 subsidized housing residents for each arm of the study. This is the population of approximately 12 subsidized housing buildings. We will therefore require a minimum of 12 pairs (intervention-control) of buildings; 6 pairs will be in Ontario and 6 will be in Quebec. This number is feasible based on our pre-implementation discussions with the housing providers in both provinces.

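### The GEE for quality of life and QALYs rests on 12–14 buildings with no small-sample adjustment stated; with the usual normal reference, its nominal 5% test rejects about 7–10% of the time

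*Protocol article*

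**What the plan says.** The Quantitative data section assigns one method to the individual-level secondary outcomes, quality of life and QALYs: the trial will "analyze the data using generalized estimating equations (GEEs) assuming an exchangeable correlation structure to adjust for clustering within a building". It names no variance estimator, no reference distribution and no finite-sample correction. It does fix five imputations, a 5% missingness trigger and the software version.

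The number of clusters follows from other sections. Under Data collection, the EQ-5D-5L is "administered by a research assistant or volunteer to all residents of intervention buildings who attend a CHAP session". Study aims and the outcome list define the contrast as attendees against their own baseline. Each intervention building is therefore one cluster. The Sample size section says "We will therefore require a minimum of 12 pairs (intervention-control) of buildings", which gives 12 clusters. The abstract says "All residents of 14 matched pairs (intervention/control) of apartment buildings will be included", which gives 14.

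**The concern.** Standard GEE inference relies on a large number of clusters, whatever the number of people in each. With 12 or 14 clusters two things go wrong. The plain sandwich variance is biased downward, because residuals are taken around an estimated mean. The Wald statistic is also referred to a normal distribution, although its variance has been estimated from about a dozen independent units. Both errors act in the same direction: intervals are too short and the test rejects too often. At stake are the reported precision of the change in EQ-5D-5L and QALYs and any statement that this change is statistically significant.

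**Working it through.** **Plan's own figure.** The article gives no error rate, power or sample size for this analysis. The only relevant figure is the alpha in the Sample size section ("Using a power of 0.8 and an alpha of 0.05"), stated for the primary outcome and without sidedness. I take a two-sided 5% test. The primary sample size is not an input here.

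**Inputs.** G = 12 (Sample size) or G = 14 (abstract). Model: an intercept-only exchangeable GEE on within-person change scores, clustered by building.

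**Equal-sized buildings, exact result.** The GEE estimate is the mean of the G building means. With s² the sample variance of those means, the uncorrected sandwich variance is Σ(ȳ_g − ȳ)²/G² = [(G − 1)/G] × s²/G. The z-test thus rejects when |t(G−1)| > 1.96 × √((G − 1)/G).

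- G = 12: √(11/12) = 0.957, threshold 1.96 × 0.957 = 1.88, true size 8.7%.
- G = 14: √(13/14) = 0.964, threshold 1.96 × 0.964 = 1.89, true size 8.1%.

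**Where the excess comes from.** Multiplying the variance by G/(G − 1) removes the standard-error bias (4.3% at G = 12, 3.6% at G = 14) but keeps 1.96. The size is then P(|t(G−1)| > 1.96) = 7.6% (G = 12) or 7.2% (G = 14).

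- G = 12: of 3.7 points of excess (8.7 − 5.0), 2.6 come from the normal reference (7.6 − 5.0) and 1.1 from the standard error.
- G = 14: of 3.1 points (8.1 − 5.0), 2.2 come from the reference and 0.9 from the standard error.

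The t quantiles that should replace 1.96 are 2.20 (11 df) and 2.16 (13 df).

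**Other variance choices.** Simulated model-based standard errors with z, equal buildings, give 8.5–8.7% (G = 12) and 7.9–8.2% (G = 14). Choosing model-based over robust errors therefore does not solve the problem.

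**Unequal buildings, simulated.** The Inclusion and exclusion criteria allow 50–200 units, so cluster sizes will differ. The spread of attendee numbers and the ICC for change in EQ-5D-5L are not in the article. One set of assumptions is one resident per unit, 10–40% attendance, 60% retained (from the 40% loss under Control of bias and loss to follow-up) and an ICC of 0.01–0.07. The article's 0.07 belongs to the primary outcome.

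| Analysis, unequal buildings | True size, G = 12 to 14 |
|---|---|
| Uncorrected sandwich, z | 8.2–9.6% |
| G/(G − 1) factor, z | 7.2–8.3% |
| Kauermann-Carroll, t(G − 1) | about 5.0–5.6% |
| Mancl-DeRouen, t(G − 1) | 4.2–4.7% |
| One-sample t-test on building means | 4.9–5.3% |

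A harsher simulation re-estimated the working correlation in every run and let it go negative. The uncorrected z-test then had size 10.2–12.2% (G = 12) and 9.2–10.6% (G = 14). The simple G/(G − 1) factor with t gave 6.3–8.1% and 5.9–7.4%. I do not rest the headline on this, because it depends heavily on the assumed spread of cluster sizes and on a small ICC.

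**Width of a corrected interval.** 2.20/1.96 × √(12/11) = 1.17 and 2.16/1.96 × √(14/13) = 1.14, that is, 14–17% wider.

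**The case against.** The strongest reply is that silence is not a wrong choice. The article never says the variance is uncorrected or the reference normal, a condensed article commonly leaves such detail to the analysis plan, and that plan is not shown. This stands in part. A reader might infer that the trial has decided against a small-sample correction, or that its error bars are certainly wrong. The text supports neither, and with a correction and a t reference the test holds close to 5%. What remains is that the article commits to a large-sample method on 12–14 clusters, and the method run as described misses its nominal level.

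Four further points limit the claim.

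- **Imputation.** With 40% loss expected and a 5% trigger, multiple imputation is close to certain. Pooling brings its own between-imputation variance and reference distribution, which were not modelled.
- **Scope.** A reader might extend the point to blood pressure, BMI, waist circumference and CANRISK. The article assigns the GEE only to quality of life and QALYs, so that extension has no textual basis.
- **Cluster count.** The section on bias speaks of losses being similar in both arms, which could suggest that control residents are also measured. No such collection is described. If it took place (24–28 clusters, two arms), the uncorrected size would still be 7.0–7.4%.
- **Importance.** The outcome is a secondary, uncontrolled change among voluntary attendees. The randomized comparison does not depend on it.

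**Conclusion.** The point holds in a conditional form. For quality of life and QALYs, a GEE on 12–14 buildings with the usual normal reference has a true size of about 7–10% at a nominal 5%. The lower end is a simple variance factor with z; the upper end is an uncorrected sandwich with unequal buildings. The anchor figures, 8.7% and 8.1%, are exact for equal-sized buildings under the model shown. The main cause is 1.96 in place of 2.16–2.20, with standard errors about 4% too small as the lesser cause.

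The result assumes a two-sided test of mean change, data from intervention buildings only, and no multiple imputation. The unequal-building figures also rest on assumed attendance and ICC. It would be wrong to read this as a defect in the trial's main result: the primary outcome uses a building-level ANCOVA and is not touched.

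**What to change.** Keep the GEE and add one sentence, before the data are analysed, naming a bias-corrected sandwich variance and a t reference on (buildings minus 1) degrees of freedom. Kauermann-Carroll comes close to 5%; Mancl-DeRouen is slightly conservative. State also how this reference is combined with the pooling of imputed datasets.

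The alternative is to compute each building's mean change and apply a one-sample t-test across buildings. It needs no special software, involves no working correlation and held its level in the unequal-building simulations. Its price is that small and large buildings count equally, so it estimates the average building's change and not the average attendee's.

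Either way the cost is intervals about 14–17% wider than uncorrected ones. Data collection and the primary analysis do not change.
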